**Figure 1 f1:**
[figure not shown]
A conceptual framework for the CarMeR Study.

This project, dubbed the Cardiometabolic Risks (CarMeR) Study, is by the Bill and Melinda Gates Foundation through the African Postdoctoral Initiative, managed by the African Academy of Sciences. The objectives are: 1. determine the prevalence of undiagnosed diabetes, prediabetes and other associated cardiovascular disease risks using the multi-sampled oral glucose tolerance test [OGTT] with 82.5g monohydrate dextrose, 2. characterize the phenotype of diabetes and prediabetes relative to body composition, body mass index (BMI), and other anthropometric measures, 3. establish the ocular characteristics and complications in people with diabetes and prediabetes, 4. ascertain whether the etiology of undiagnosed diabetes is predominantly insulin resistance or beta-cell insufficiency using homeostasis model analysis of beta [HOMA-β and HOMA-IR], 5. determine the sensitivity of diagnostic alternatives to the multi-sampled OGTT, specifically the fasting plasma glucose (FPG) test and the glycated hemoglobin (HbA1c) test, and 6. determine, over a 1-year period, if changes in food choices, physical activity, weight loss and psychosocial counseling influence reversal or prevention among people newly diagnosed with diabetes and prediabetes.

## Methods

The CarMeR Study will be executed by a multidisciplinary team of researchers from the University of Cape Coast, its Directorate of Health Services, the Rwanda National Hospital, and the University of Global Health Equity, Rwanda. To obtain reliable and valid results, the CarMeR Study will adhere to gold standards in all aspects of the project, including but not limited to the selection of communities, standardization of study protocols, adherence to ethical principles in the sampling procedures, anthropometric measurements, blood glucose testing, chemistry measurements, eye examination, blood pressure measurements, and surveys. The CarMeR Study will adopt the WHO-STEPwise approach for assessing cardiometabolic risk factors The STEPwise approach to surveillance (STEPS) is an NCD surveillance tool recommended by the WHO since 2005 for monitoring trends across countries (38, 39). The WHO-STEPwise instrument comprises three distinct phases or “steps” for evaluating risk factors. The first step is a questionnaire-based assessment, the second step comprises of physical measures and the third step comprises of biochemical measures (40). This instrument is a simplified and standardized approach to surveillance for collecting, analyzing and disseminating data on key risk factors especially for NCDs (38). In addition to a questionnaire survey, a community-based quasi-experimental design will be utilized to assess the glucose tolerance of all participants after administration of 82.5g monohydrate dextrose, in order to ascertain the prevalence and risk factors for undiagnosed diabetes and prediabetes. Subsequently, all consenting participants diagnosed with abnormal glucose tolerance will be enrolled into a community-based randomized controlled trial (RCT) to measure the effectiveness of lifestyle interventions on diabetes remission.

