**Methods and analysis:**

The study employs a community-based quasi-experimental design, making use of pre- and post-intervention data, as well as a questionnaire survey of 1200 individuals residing in the Cape Coast metropolis to ascertain the prevalence and risk factors for undiagnosed diabetes and prediabetes. Physical activity, dietary habits, stress levels, sleep patterns, body image perception, and demographic characteristics will be assessed. Glucose dysregulation will be detected using oral glucose tolerance test, fasting plasma glucose, and glycated hemoglobin. Liver and kidney function will also be assessed. Diabetes and prediabetes will be classified using the American Diabetes Association criteria. Descriptive statistics, including percentages, will be used to determine the prevalence of undiagnosed diabetes and cardiovascular risks. Inferential statistics, including ANOVA, t-tests, chi-square tests, ROC curves, logistic regression, and linear mixed model regression will be used to analyze the phenotypic variations in the population, ocular characteristics, glycemic levels, sensitivity levels of diagnostic tests, etiological cause of diabetes in the population, and effects of lifestyle modifications, respectively. Additionally, t-tests will be used to assess changes in glucose regulation biomarkers after lifestyle modifications.

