#### Inclusion criteria

Participants would be included in the study if they aged 25 to 70 years, and have not been diagnosed with prediabetes or diabetes. Additionally, participants should be willing to undergo the screening procedure (glucose testing, eye examination, BMI assessment, lipid level measurement, and body composition analysis). Participants diagnosed of diabetes based on a 2-hour OGTT glucose level between 11.1-17.0mml/L (200-300mg/dL) or prediabetes with 2-hour OGTT glucose level between 7.8-11.0 mmol/L (140-199mg/dL), would be followed up with a non-pharmacological lifestyle intervention for one year to assess the effect on their glucose tolerance.

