#### Diagnoses

Diagnosis of abnormal glucose tolerance in the CarMeR study will be done using fasting plasma glucose (FPG), HbA1c and OGTT diagnostic tests based on the criteria suggested by the International Experts Committee Report on Diabetes and American Diabetes Association (59, 60). Participants are classified as having prediabetes if they have an FPG level between 5.6mmol/L and 6.9 mmol/L (100mg/dl and 125mg/dl), or an HbA1c level between 5.7% and 6.4% or a 2-hour OGTT result between 140mg/dl and 199mg/dl. Participants are classified as having diabetes if they have an FPG level of 7.0 mmol/L or higher (126mg/dl or higher), or HbA1c level of 6.5% or higher, or a 2-hour OGTT result of 200mg/dl or higher. Additionally, 1-hour post load plasma glucose (PG) will be used to diagnosed hyperglycemia (IH) and diabetes. Participant with a 1-h PG ≥ 155 mg/dL (8.6 mmol/L) are considered to have IH and should be prescribed lifestyle interventions and referred to a diabetes prevention program. Participants with a 1-h PG ≥ 209 mg/dL (11.6 mmol/L) will be considered to have diabetes. Generalized obesity is defined as body mass index (BMI) ≥30 kg/m^2^, and central obesity as a waist circumstance >102 cm in men or >88 cm in women, and a waist-to-hip (WHR of 0.88-0.89 (61, 62). Certified medical laboratory diagnostic scientists will perform all blood sample analysis at the Cardiometabolic Epidemiology Research Laboratory (CERL).

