### Enrollment visit

Prior to data collection, recruitment of participants is done by the research assistants (RAs). This is achieved through community engagement via the identified gatekeepers of the specific community. The gatekeepers subsequently organize their community members to engage with the research team. The RAs recruit eligible participants based on the inclusion criteria. The selected participants are assigned codes to anonymize them, and their contacts are collected. Participants who meet the inclusion criteria and agree to participate in the study are asked to sign an informed consent form. Prior to the day of the data collection, participants are called on phone and are reminded of the requirement to fast (8-12 hours), and not ingest any other fluid apart from water. Participants arrive at the study site at 6:30am as communicated to them, and they are asked to rest for a while before their vital signs were measured. Anthropometric measurements are taken, followed by baseline blood samples for FBG, creatinine, liver function tests (AST and ALT), and lipid profiles. After which, a three-point OGTT is performed to assess glucose tolerance. The whole and plasma blood samples are then sent to the CERL at University of Cape Coast, Ghana for analysis and preservation in a cryogenic freezer -40°C. The entire duration of the process is expected to last four hours. Subsequently, participants newly diagnosed with diabetes using a 2-hour glucose level between 11.1-17.0mmol/L (200-299mg/dL) are put into one cohort to complete 12 months lifestyle intervention program and monthly follow-ups. While participants identified with 2-hour glucose ≥ 17.0mmol/L (≥300mg/dL) are referred for medical treatment.

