### Data analysis

For the accuracy of data and information, data collected through the Kobo Collect toolbox application will be downloaded into an Excel spreadsheet and screened visually and statistically. Data will be analyzed and interpreted by the principal investigator and his local collaborators and shared back with foreign collaborators. In the attempt to make the findings of the study public, data analysis will be conducted using STATA 16 and SPSS 23. Statistical tools specific and relevant to the research questions and hypotheses of the CarMeR study would be used. To determine the prevalence of undiagnosed diabetes, prediabetes and other associated cardiovascular risks, data on OGTT, FPG and HbA1c will be analyzed using descriptive statistics (percentages and confidence intervals). In order to investigate the differences in phenotype, diabetes, prediabetes, and normoglycemic groups will be compared based on BMI and body composition (waist hip ratio, body fat percentage, skeletal muscle, total body water) using analysis of variance (ANOVA) and t-test. To profile the ocular characteristics and complications of the diabetes and prediabetes groups, a cross-tabulation and a subsequent chi-square test will be done to assess the association between glycemic dysregulation and the presence of ocular complications (diabetic retinopathy, cataract, macular edema). For the purpose of ascertaining whether the predominant etiological factor of undiagnosed diabetes in this populations is insulin resistance or beta-cell failure, a homeostasis model analysis of beta [HOMA-β and HOMA-IR] will be computed and logistic regression will be used to determine the dominant factor. As a way of determining the sensitivity of other diagnostic alternatives (FPG and HbA1c) in comparison to the multi-sampled OGTT, receiver-operated characteristics (ROC curves), including sensitivity and specificity curves, will be used. Finally, to ascertain whether lifestyle changes (food choice, physical activity, weight loss, psychosocial counseling) over a one-year period impacts biomarkers of glucose regulation, a linear mixed model regression analysis, controlled for baseline characteristics will be used. T-tests will be conducted to observe changes in glucose regulation biomarkers.

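### The one-year lifestyle phase is called a randomised controlled trial in one section and described as uncontrolled follow-up in others; in the uncontrolled form, objective 6 cannot separate an intervention effect from regression to the mean

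*Protocol article*

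**What the plan says.** The article describes the one-year phase in four places.

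- **Methods, opening paragraph:** after glucose testing, "all consenting participants diagnosed with abnormal glucose tolerance will be enrolled into a community-based randomized controlled trial (RCT)". The stated purpose is to measure effectiveness on diabetes remission.
- **Abstract, Methods and analysis:** "The study employs a community-based quasi-experimental design, making use of pre- and post-intervention data".
- **Inclusion criteria:** people with 2-h OGTT glucose of 11.1-17.0 mmol/L (diabetes) or 7.8-11.0 mmol/L (prediabetes) "would be followed up with a non-pharmacological lifestyle intervention for one year to assess the effect on their glucose tolerance".
- **Enrollment visit:** participants newly diagnosed with diabetes in the 11.1-17.0 mmol/L band "are put into one cohort to complete 12 months lifestyle intervention program and monthly follow-ups".

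Objective 6, in the list after Figure 1, asks whether lifestyle changes "influence reversal or prevention among people newly diagnosed with diabetes and prediabetes". Expected outcomes speaks of efficacy in preventing or reversing disease.

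For this objective, Data analysis names a linear mixed model adjusted for baseline characteristics and adds that "T-tests will be conducted to observe changes in glucose regulation biomarkers". The abstract places those t-tests after the lifestyle modifications.

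**The concern.** Whether a concurrent control group exists is the basic design fact of an intervention phase, and the article gives incompatible accounts of it. An analysis plan cannot settle this later, because it decides how participants are allocated and what they receive.

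The conflict matters because entry is defined by a high value of the quantity on which benefit will be judged. Among people chosen because one 2-h reading was high, some were high by chance on that day, and their next reading tends to be lower. A randomised control arm shares this fall, so it cancels in the between-arm difference. A single cohort has nothing to subtract it from, and adjusting for baseline within one cohort does not remove it. Effectiveness, efficacy and reversal could then be claimed from a change that would have occurred with no intervention effect.

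**Working it through.** **1. The passages side by side**

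| Section | Who enters the one-year phase | Control condition |
|---|---|---|
| Methods | All consenting participants with abnormal glucose tolerance | Implied by the word randomised; not described |
| Inclusion criteria | Everyone in the 2-h diabetes and prediabetes bands, all followed up with the intervention | None mentioned |
| Enrollment visit | New diabetes cases in the 2-h band, as one cohort completing the programme | None mentioned |
| Abstract | Not stated; pre- and post-intervention data | None mentioned |

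The first row cannot hold together with the second and third. The abstract fits the uncontrolled version but does not by itself say that everyone is treated.

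**2. Plan figures for this phase**

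There are none to reproduce. The only sample-size statement (Participants: about 1000, raised to 1200) concerns prevalence. No reversal rate, SD, within-person variability or allocation ratio is given.

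**3. Regression to the mean with no intervention effect**

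Inputs from the article: entry bands 7.8-11.0 and 11.1-17.0 mmol/L; expected undiagnosed diabetes 6-7%; 1000 to 1200 participants.

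Assumed inputs: population 2-h glucose lognormal, median 6.2 mmol/L, sdlog s = 0.385. This puts 6.5% at or above 11.1, 6.1% in 11.1-17.0 and 21% in 7.8-11.1. Within-person CV is 5, 10, 15 or 20%.

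Within-person log variance: w² = ln(1 + CV²). Test-retest correlation on the log scale: ρ = 1 − w²/s², with s² = 0.148. At CV 15%, w² = 0.0223 and ρ = 0.85. The median retest value after a first reading x is 6.2 × exp{ρ ln(x/6.2)}. For x = 12.0, ln(12.0/6.2) = 0.660, times 0.85 is 0.561, and 6.2 × exp(0.561) = 10.9 mmol/L. That is already below 11.1.

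Number of diabetes cases: 1000 × 6.1% = 61; 1200 × 6.1% = 73; 1200 × 6.5% = 78. I take 60 to 78.

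Simulated test-retest pairs, entry capped at 17.0:

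| CV | ρ | Diabetes group, retest < 11.1 | Prediabetes group, retest < 7.8 | Mean change, diabetes group (mmol/L) | Paired t-test significant, n = 60-78 |
|---|---|---|---|---|---|
| 5% | 0.98 | 15% | 12% | −0.1 | about 20-25% |
| 10% | 0.93 | 30% | 23% | −0.5 | about 60-70% |
| 15% | 0.85 | 44% | 34% | −1.1 | about 91-96% |
| 20% | 0.74 | 58% | 43% | −1.9 | about 99-100% |

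Hand check of the last column at CV 10%, n = 60, with a simulated SD of change of 1.74: 0.50 × √60 / 1.74 = 2.23, and Φ(2.23 − 1.96) = 0.61.

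In the prediabetes group the paired-test rates at n = 78 are lower, about 20/38/60% at CV 10/15/20%.

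**4. Other assumptions**

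With population mean 6.5-7.0, SD 2.0-2.5, normal or lognormal, and test-retest correlation 0.5-0.9, 36-87% of the diabetes group and 21-57% of the prediabetes group fall below their cut-offs. Some of these settings put far fewer than 6-7% in the diabetes band, so they fit the article less well than the calibrated set above.

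**The case against.** The strongest reply is that this is a condensed article on a two-phase study. Arms, allocation and model terms are commonly left to the full protocol or analysis plan. Methods attaches the quasi-experimental label to the glucose-testing stage and introduces the trial as a later step, and a randomised trial also has pre- and post-intervention data. One cohort in the enrolment section may only separate new diabetes cases from those referred for medical treatment.

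Much of this stands, and it rules out several stronger readings that a reader might infer.

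- *The analysis excludes a between-arm comparison.* Data analysis is silent on arms. It does not say that the t-tests are paired, and the mixed model could carry an arm term.
- *A control arm is impossible because people with raised 1-h glucose* "are considered to have IH and should be prescribed lifestyle interventions and referred to a diabetes prevention program". No 1-h distribution is given, so the share affected is unknown, and such advice or referral need not be the study's own programme.
- *The result will be reported as reversal.* That predicts later interpretation. The article announces the aim, not the conclusion.
- *All glucose markers are equally affected.* Selection is on 2-h glucose. The fall in FPG and HbA1c would be smaller and was not computed.

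The reply does not remove the conflict between Methods and the inclusion criteria, which give the intervention to everyone in both bands. That is contradictory text, not omitted detail.

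**Conclusion.** The concern holds as an internal contradiction with a conditional consequence. The article promises a randomised trial and also describes an uncontrolled phase, mentions no control condition, and names no between-arm contrast for objective 6.

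If the uncontrolled version is followed, the direction of the bias in 2-h glucose is certain: it favours apparent improvement. Its size is not fixed by the documents. At an assumed within-person CV of 10-20%, between 30 and 58% of the diabetes group and 23 to 43% of the prediabetes group would cross below their entry cut-off with no effect. A paired test in 60-78 diabetes cases would then be significant in about 60% to nearly all studies, against about 20-25% at CV 5%. Claims of effectiveness, efficacy or reversal would not be supported.

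If a randomised control arm does exist and is the basis of the comparison, this consequence falls away and only the text needs correcting. The prevalence objectives are untouched either way.

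**What to change.** Make the abstract, Methods, Inclusion criteria, Enrollment visit and Data analysis describe one design, and check the 1-h glucose statement in Diagnoses for consistency with it.

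- **If there is a randomised control arm:** state it. Make the baseline-adjusted between-arm difference at 12 months, including the proportion reverting, the test for objective 6. Keep within-group change as description only.
- **If there is no control arm:** delete the terms RCT, effectiveness and efficacy for this phase. Restate objective 6 as uncontrolled before-after change, and report it with a caution on, or an estimate of, regression to the mean.

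The change is to wording and analysis text. Without a control arm, the price is a weaker claim for objective 6. With one, the roughly 60-78 expected diabetes cases would be divided between arms. The article gives no effect size, SD or allocation ratio from which to judge whether that is enough, so nothing can be said here about whether more participants are needed.

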### Population

The population comprises adults aged between 25 and 70 years living in households within the Cape Coast metropolis. The choice of this age range was influenced by the fact that they are at a higher risk of developing diabetes in the metropolis (41, 42). It is estimated that the number of people between the ages of 25 and 70 living in the Cape Coast Metropolis is 102,533 (43), spread across several households and communities in the metropolis. The sample for the study is being drawn from rural, peri-urban, and urban communities in the Cape Coast Metropolis. Owing to the heterogeneous nature of the Cape Coast population, the selection of participants for this study is based on different characteristics. These characteristics includes the type of community (rural, peri-urban, urban), main economic activity (farming, fishing, trading, formal work), dominant religion (Christianity, Islam, African traditional religion), and ethnicity (Fante, Ewe, Asante, northern tribes).

### Participants

Following the protocol of the Research on Obesity and Diabetes among African Migrants (RODAM) study, which focused on obesity and type 2 diabetes among African migrants (44), this study estimates the prevalence of undiagnosed type 2 diabetes (T2D) in the Cape Coast metropolis of Ghana, at 6-7%, and the prevalence of obesity at 17%. The study aims for a power of 0.90 with α=0.05, including the Bonferroni correction. Using these parameters, a sample size of approximately 1000 would be sufficient to detect a 10% proportion of undiagnosed T2D. In order to compensate for attrition, the study seeks to recruit 1200 self-identified healthy individuals from 13 urban and rural communities in the Cape Coast Metropolis, who have not been previously diagnosed of diabetes or prediabetes prior to the study for collection of baseline data.

Due to the large and geographically dispersed population, a multistage sampling technique would be employed to sample participants for this study. This will be done in three stages, where the first stage involves dividing the population into clusters, based on the already existing communities within the metropolis. The second stage involves sampling these clusters to be used in the study by using systematic random sampling. At this stage, 13 clusters representing 13 rural, peri-urban and urban communities would be selected for the subsequent sampling stage. Finally, the third stage would involve further sampling within each selected cluster to randomly select households, and recruit the first two persons from each family line (with random replacement) in the indigenous communities, while using convenience sampling in non-indigenous communities. It is envisaged that approximately 90-100 participants will be randomly selected from three rural communities (Efutu Mampong, and Efutu), four fishing communities (Abekam, Duakor, Ekon, and Ntsen), three peri-urban communities (Ayeko-Ayeko, Ankaful and Nkanfoa) and one urban community (UCC), two market communities (Kotokuraba and Abura Markets), and one artisanal community (Siwdu). Household mapping will be done utilizing the 2021 Housing Census Data. All the 1200 volunteers will be recruited from their communities of origin before disclosing any monetary benefits.

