## Introduction

Research has established that obesity, high levels of glucose, and triglycerides are significant contributors to the risks of developing cardiometabolic diseases [CMDs] (1–4). However, literature suggests that two-thirds of African-born individuals in sub-Saharan Africa living in America diagnosed with abnormal glucose tolerance are more likely to be non-obese (5). This has led to research to establish the specific causes of diabetes and prediabetes in an African population, and to identify risk factors unique to Africans. The main mechanisms for the development of diabetes are beta-cell failure and insulin resistance, with abnormal glucose tolerance representing an imbalance between the degree of insulin resistance and the β-cell secretion (6–8). Identifying the etiology of diabetes is critical for prescribing the relevant treatment or interventions (6).

Globally, 537 million adults live with diabetes, with Africa contributing 4.47% (24 million) and witnessing 416,000 diabetes-related deaths in 2021 alone (9). According to the International Diabetes Federation (9), this prevalence is projected to double by 2045 due to high rates of abnormal glucose tolerance, including prediabetes (5, 10–12). Prediabetes and diabetes represent a glycemic continuum with both associated with vascular complications and an increased burden on all-cause mortality rates. Presently, 179.2 million individuals globally with undiagnosed diabetes (13), with the IDF Africa Region standing out with the highest rate of undiagnosed cases among all IDF regions, at 60% (14). This underscores the critical need for increased awareness, early detection, and intervention strategies to address undiagnosed diabetes in Africa.

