Early diagnosis of diabetes is crucial for mitigating its debilitating effects, including peripheral neuropathy, retinopathy, diabetic foot complications, and the susceptibility to infectious diseases (17, 19, 20). The estimated prevalence of diabetes in Ghana is 6.5% (21), suggesting that one in every 15 Ghanaians has diabetes, signifying the onset of a worrying epidemic. Diabetes is a major contributor to mortality in Ghana, with 9,778 deaths reported in 2017, up from the 8528 in 2014 (22). The cost of treating one person with diabetes in Ghana as at 2017 was a high $106.5. Diabetes is reaching epidemic proportions in sub-Saharan Africa, with the region experiencing the most rapid increase in type 2 diabetes (T2D) worldwide and the highest proportion undiagnosed diabetes (9). To address this epidemic and its complications, comorbidities and mortalities, measures must encourage the early diagnosis of diabetes and reduce undiagnosed diabetes (9). Identifying and developing African-specific tools and interventions to improve the early diagnosis of diabetes and prescribe effective treatments requires more clinical research in the African population. The prospective findings of this research should be incorporated into the clinical care of prediabetes and diabetes, and replicated across many African countries in both rural and urban areas. Given that Ghana has a typical African population and an epidemic-like prevalence of diabetes (21), data from this study can bridge developing and developed countries, increasing the degree of certainty of data extrapolation and modeling of diabetes-related prevalence and outcomes.

The increased susceptibility to diabetes in people from lower- and middle-income countries has been well explored (9, 23–25). In Ghana, the extent to which obesity phenotypes, dietary habits, socioeconomic status, perceived stress, sleep patterns, geographical location, and occupational characteristics contribute to cardiometabolic risk development has not been well explored (26–30), especially due to diagnostics and methodological limitations. There is still a dearth of data concerning the actual prevalence of undiagnosed diabetes in Ghana, the specific interventions to remedy these risk factors, and how culturally sensitive non-pharmacological interventions such as diet and physical activity can contribute to diabetes remission in newly diagnosed persons with abnormal glucose tolerance.

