### Data collection procedures

This is a community-based study, and data collection will be done at the community centers of each community. Data collection is expected to last for five months and the data collection sites for this study include community centers, households, churches and mosques. This will be done after permission is obtained from the gatekeepers in the community for community entry. The gatekeepers include, but not limited to traditional chiefs, opinion leaders, imams, pastors and assembly members. After satisfying all the requirements, ethical clearance for this study has been obtained from the University of Cape Coast (UCC) Institutional Review Board (IRB) with the number UCCIRB/EXT/2022/27. Data will be collected from two or more participants in a single household. For fair representation, participants aged ≥ 25 years will be randomly selected from each household. The purpose of the study, including the benefits and the risks involved will be clearly explained to the participants. After which verbal and written consent will be sought from the prospective participants who have agreed to participate in the study. Written and verbal informed consent will be obtained from each participant for each part of the study, including the survey questionnaires, anthropometric measurements, eye examination and biochemical sample collection.

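### The stated power of 0.90 with about 1000 people ignores the article's own cluster and household sampling, and no clustering is named for the prevalence interval

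*Protocol article*

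**What the plan says.** The Participants section plans on this prevalence: "this study estimates the prevalence of undiagnosed type 2 diabetes (T2D) in the Cape Coast metropolis of Ghana, at 6-7" per cent. It then sets the operating characteristics, "The study aims for a power of 0.90 with α=0.05, including the Bonferroni correction", and concludes that "a sample size of approximately 1000 would be sufficient to detect a 10% proportion of undiagnosed T2D". The only increase, from about 1000 to 1200, is for attrition.

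The same section describes multistage sampling: "13 clusters representing 13 rural, peri-urban and urban communities would be selected for the subsequent sampling stage". It envisages about 90 to 100 people per community, takes two people from each family line in indigenous communities, and uses convenience sampling in non-indigenous ones. Data collection procedures adds: "Data will be collected from two or more participants in a single household".

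For prevalence, Data analysis says that "data on OGTT, FPG and HbA1c will be analyzed using descriptive statistics (percentages and confidence intervals"). It names ANOVA, t-tests, chi-square tests and logistic regression for the other baseline questions. A linear mixed model is named only for the one-year lifestyle question, with no community or household effect mentioned.

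**The concern.** The sample-size statement and the sampling design stand in one section but do not fit each other. People from one community, and more so from one family or household, tend to resemble each other in diabetes risk, so 1000 people from 13 communities carry less information about prevalence than 1000 independent people. The article gives its own reasons to expect this. The Population section bases selection on community type, economic activity, religion and ethnicity, and the Introduction treats social, economic and familial factors as drivers of risk.

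Prevalence of undiagnosed diabetes is what the Exclusion criteria section calls the primary objective, and the Introduction hopes that the data will support extrapolation and modelling. An interval that is too narrow would be carried into that use. A later analysis plan could correct how the interval is computed, but it could not restore precision that the sample lacks.

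**Working it through.** **Inputs from the article:** prevalence 6 to 7%, target 10%, power 0.90, alpha 0.05 with an unspecified Bonferroni correction, N about 1000 (recruit 1200), 13 clusters. **Assumed:** community ICC of 0.005 to 0.05, a one-sample two-sided test, and a Bonferroni divisor of 1 or 2.

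**1. Reproducing about 1000.** For independent observations,

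n = [z(1−α/2)·√(p0(1−p0)) + z(0.90)·√(p1(1−p1))]² / (p1−p0)².

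With p0 = 0.07, p1 = 0.10 and α = 0.025: (2.2414 × 0.25515 + 1.2816 × 0.30)² / 0.03² = (0.57189 + 0.38447)² / 0.0009 ≈ 1,016. The other readings are:

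| p0 | α = 0.05 | α = 0.025 |
|---|---|---|
| 6% | 451 | 525 |
| 6.5% | 615 | 717 |
| 7% | 869 | 1,016 |

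A two-group comparison of 6 to 7% with 10% would need 1930 to 3628 people in total, so it is not the basis. The match at 7% and 0.025 is good but not unique.

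**2. Adding the communities.** Design effect DE = 1 + (m−1)·ICC with m = 1000/13 = 76.9, and effective n = 1000/DE. Power is Φ{[(p1−p0)·√(effective n) − z(1−α/2)·√(p0(1−p0))] / √(p1(1−p1))}, shown for α = 0.025.

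| ICC | DE | Effective n | Power, p0 = 7% | p0 = 6.5% | p0 = 6% |
|---|---|---|---|---|---|
| 0 | 1.00 | 1000 | 0.895 | 0.97 | 0.99 |
| 0.005 | 1.38 | 725 | 0.78 | 0.90 | 0.97 |
| 0.01 | 1.76 | 568 | 0.68 | 0.83 | 0.92 |
| 0.02 | 2.52 | 397 | 0.53 | 0.69 | 0.81 |
| 0.05 | 4.80 | 209 | 0.32 | 0.44 | 0.56 |

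**3. How much ICC each reading tolerates.** Power stays at 0.90 while 1000/DE is at least the n of step 1. The limits are ICC 0.016 (6%, α 0.05), 0.012 (6%, 0.025), 0.008 (6.5%, 0.05), 0.005 (6.5%, 0.025) and 0.002 (7%, 0.05). There is no slack at 7% and 0.025. At ICC 0.02 power lies between 0.53 and 0.87 over all six readings.

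**4. If all 1200 are analysed.** At 7% and α = 0.025, power is 0.83, 0.73, 0.56 and 0.33 for the four ICCs. The gain is small because the extra people join the same 13 clusters: effective n cannot exceed 13/ICC, which is 650 at ICC 0.02 and 260 at 0.05.

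**5. The prevalence interval.** If it is computed as for a simple random sample, its coverage is about 2Φ(1.96/√DE) − 1: 90%, 86%, 78% and 63% for ICC 0.005, 0.01, 0.02 and 0.05. At 6.5% and N = 1000 the simple-random half-width is 1.96·√(0.065 × 0.935/1000) = 1.5 points. With the design effect and t on 12 degrees of freedom (2.179), 2.179·√(0.065 × 0.935 × DE/1000) gives 2.0, 2.3, 2.7 and 3.7 points.

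**6. Household pairs alone.** With two per household and an assumed within-pair ICC of 0.05 to 0.30, DE is 1.05 to 1.30, and power at 7% and α = 0.05 is 0.92 to 0.87. The community level matters more.

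**The case against.** The strongest reply has four parts.

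- **The shortfall is conditional.** No ICC is in the article, and neither are the test, its sidedness and the Bonferroni divisor. At 6 to 6.5%, 1000 people keep power at 0.90 for a small ICC. This stands. A reader might infer that the stated power is simply not delivered, but the article supports only that it was claimed without allowing for clustering.
- **The interval method is not specified.** Percentages with confidence intervals need not mean simple-random variance, and a condensed article may leave that choice to an analysis plan. This also stands, so the coverage figures hold only if the intervals ignore clustering.
- **The power sentence drives no planned test.** Objective 1 is estimation, and Data analysis plans no comparison with 10%. True, and this is a reason to state precision in place of power.
- **The group comparisons are less exposed.** A reader might infer that every ANOVA, t-test and chi-square test has an inflated type I error. The article does not support that. Glycaemic groups are mixed within communities, so the factor is nearer 1 + (m−1)·ICC(group)·ICC(outcome). With m = 77 and both ICCs at 0.01, 0.02 or 0.05 it is 1.01, 1.03 or 1.19. A simulation of 13 communities of 77, without household pairs, gave rejection rates of 5.2%, 5.3% and 6.9% at nominal 5%.

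A reader might also multiply the national 6.5% by the 60% undiagnosed share, both in the Introduction, to get 3.9%, and call the 6 to 7% planning value wrong. That mixes a Ghanaian figure with one for the whole IDF Africa Region, whereas the planning value is for Cape Coast adults in an age range chosen as higher risk. It would also work against the power concern: 3.9% against 10% needs only 180 independent people at α = 0.025.

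**Conclusion.** The point holds in a limited form. The power of 0.90 is stated without regard to the community, family-line and household sampling in the same article, and the only inflation is for attrition. The direction is certain for any positive ICC; the size is not.

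At 7%, almost any positive ICC takes power at 1000 below 0.90. At 6 to 6.5% there is room up to about 0.005 to 0.016. At 0.02 no reading tried at alpha 0.05 or 0.025 reaches 0.90. For the prevalence estimate, the realistic half-width at 6.5% is about 2 to 4 points against 1.5 for a simple random sample. These figures rest on an assumed ICC of 0.005 to 0.05, equal cluster sizes, and 13 unstratified clusters. Unequal weights or household clustering would generally widen the interval further, and using communities as strata could narrow it.

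**What to change.** In Participants, state the assumed ICC or design effect and its source. Replace the power sentence with the precision that 13 clusters can give: about 2 to 4 points either side at 6.5% for ICC 0.005 to 0.05, using t with 12 degrees of freedom.

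In Data analysis, say that prevalence intervals treat community as the primary sampling unit and use cluster-based degrees of freedom. Stata, which the article already names, can do this. If community types are made strata, single-community types (urban, artisanal) must be combined with others, and the degrees of freedom fall below 12. For the comparisons and regressions, name cluster-robust errors or a community random effect, with a household effect where households were sampled.

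State also that none of this repairs selection bias from convenience sampling in the non-indigenous communities.

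The cost is a less favourable stated precision and small changes to the analysis code. Nobody extra has to be enrolled.
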